**Public Title: Protocol: Effectiveness of a health-related social needs clinical decision support system**

**Contact for Public Queries:** [name], PhD

[name], [contact]

[[contact]](mailto:[contact])

**Contact for Scientific Queries:** [name], MPH

[name], [contact]

[[contact]](mailto:[contact])

**Funding:** Agency for Healthcare Research & Quality (1R01HS028008; PI: [name]).

**Primary sponsor:** Indiana University (responsibilities: trial registration, initiation, and study management)

**Countries of Recruitment:** United States

**Health Condition(s) or Problem(s) Studied:** Health-related social needs (HRSNs)

**Trial Identifier & Registry Name:** ClinicalTrials.gov Identifier: NCT06655974. Predictive Modeling for Social Needs in Emergency Department Settings. Date of the registration: 10/22/2024

The Indiana University Institutional Review Board approved the study: #2011558232 (Date of approval: 12/14/2020)

**Protocol Version:** 02/19/2025

1. **Rationale & Objectives**

Health-related social needs (HRSNs) encompass various non-medical risks from a patient’s life circumstances. Since the emergency department (ED) is a crucial yet challenging setting for recognizing and addressing patient HRSNs, a clinical decision support (CDS) intervention could assist in identifying patients at high risk of having HRSNs. This project will implement and evaluate a CDS intervention that informs ED clinicians about which patients are likely to screen positive for an HRSN. Identifying patients with HRSNs is the essential first step in effectively addressing HRSN. Currently, in the ED, patients with HRSNs are often under-identified. Identifying these patients enhances clinician awareness, allowing them to provide patient-centered care by connecting patients to the necessary services and resources to address HRSN. Ultimately, key objectives for healthcare organizations in identifying patients with HRSNs are to reduce preventable utilization and increase primary care utilization. Providing services that address HRSNs has effectively reduced repeat utilization among high-risk ED patients.

**Specific Aims and Hypotheses:**

The overall objective of this study is to improve patient care by improving the management of HRSNs. Specifically, this study will test for effectiveness of the CDS intervention at multiple points in the process from seeking care to changes in utilization with the following hypotheses:

*Hypothesis 1: Implementing a CDS intervention will increase the percentage of ED patients screened for HRSNs.*

*Hypothesis 2: Implementing a CDS intervention will increase the percentage of ED patients referred to HRSN services (based on risk prediction scores).*

*Hypothesis 3: Implementing a CDS intervention will reduce the percentage of ED patients with ED revisits (measured at 3, 7, and 30 days).*

*Hypothesis 4: Implementing a CDS intervention will increase the percentage of ED patients who have follow-up visits with primary care providers within 7 days of discharge.*

1. **Eligibility Criteria**

**Clinicians:**

- Inclusion criteria:
  - ED clinician (physician, fellow, advanced practice provider, resident) delivering care at IU Health Methodist.
  - Has access to Health Dart
  - Full and part-time
- Exclusion criteria:
  - Non-clinician
  - No access to Health Dart

**Patients:**

- Inclusion criteria:
  - Adults (≥18 years old) who seek ED care at IU Health Methodist or comparator EDs within the Indianapolis, IN MSA.
- Exclusion criteria:
- Present with a critical illness or injury (e.g., severe trauma patients or those with Emergency Severity Index (ESI) classification level 1).
- Have been transferred from another inpatient facility or died during the ED encounter.
- ED visits resulting in hospital admissions.

Recruitment status: Pending (Participants are not yet being recruited or enrolled at any site)

1. **Study Design**

The study will employ a non-randomized pre-post design with a comparison group of propensity-score matched ED patients from the same metropolitan area who were unexposed to the CDS intervention. The analytic strategy will follow a difference-in-difference (DiD) approach. The study protocol does not include blinding, masking, or random assignment. While Health Dart is available to every IU Health ED, the CDS intervention using HRSN risk scores will only be active at the IU Health Methodist ED during the study period. The Health Dart platform is accessible to clinical staff for all patient encounters. The CDS intervention will generate scores for all eligible adult patients. If risk scores cannot be produced (due to system outages or the absence of prior patient data), error messages explaining the reasons will be provided to end users. These encounters will be excluded from the analyses.

1. **Intervention**

The clinician-facing CDS intervention draws extensively on prior work describing clinician, staff, and patient use of HRSN information in the ED, those same stakeholders’ views of prediction modeling of HRSN risk identification and engineering of features relevant to measuring HRSNs, and independent development of the CDS platform. At the time of this study protocol submission, IU Health ED sites screened neither universally nor systematically for HRSNs. However, the ED was staffed with social workers to support patients with identified HRSNs.

The CDS intervention will be available to clinical end-users at the IU Health Methodist ED via an electronic platform called Health Dart. Health Dart is a FHIR-based CDS that directly integrates information from the Indiana HIE into IU Health’s Cerner EHR. Health Dart is organized as a chief complaint-focused dashboard. Health Dart summarizes recent patient information for several conditions/complaints, such as chest pain, abdominal pain, pregnancy, arrhythmia, and dyspnea. End users select the conditions/complaints to view from the navigational menu. Health Dart is single sign-on and context aware (end users do not have to log in separately from the EHR; the information displayed is for the patient being viewed in the EHR). Health Dart usage is limited to clinical staff and is voluntary.

Our intervention adds the HRSN risk prediction score as an additional condition/complaint displayed in Health Dart. End users selecting the social needs menu will be presented with a likelihood score for the following HRSNs: housing instability, food insecurity, transportation barriers, financial strain, and history of legal involvement. For each HRSN, we used Lasso models to identify a parsimonious set of predictors for logistic models. We summed the unexponentiated post-selection model coefficients to arrive at a total score. Risk prediction scores do not include race and ethnicity as inputs to avoid bias. For each HRSN, the likelihood of screening positive is reported as “high”, “medium”, or “low” by categorizing the predicted model score. To ensure demographic parity (i.e., the same rate of identifying true positives within each demographic group), we followed prior studies by adjusting score thresholds so that the sensitivities (i.e., the percentage of true positives identified by the risk score) were more equivalent within each risk score level and overall.

HRSN risk scores are triggered by patient registration at the ED. Within 20 seconds of patient registration, Indiana HIE passes an HL7 message with patient identifiers to the Regenstrief Institute’s application servers. Backend applications parse the message, apply inclusion criteria, and query the INPC database for model inputs. Model scores are expressed as FHIR resources, which Indiana HIE can use to query when an end user accesses Health Dart. Within Health Dart, after reviewing the overall score, users may select a specific HRSN to open a second panel listing all the features used to derive the score with dates. The HRSN portion of the CDS will only be accessible to clinical staff practicing at the IU Health Methodist ED (the intervention site). Indiana HIE can restrict access based on the roster of User IDs supplied by IU Health. However, clinicians practicing at other IU hospitals and IU Health Methodist could access Health Dart and the HRSN CDS.

1. **Measures and Outcomes**

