**Secondary outcomes**

3a. Percent of encounters with an ED revisit measured at 3 days. The numerator will be an ED encounter at any facility included in the INPC database within 3 days of an ED encounter at an intervention or comparator site. ED revisits may serve as the index visit for subsequent revisits. The denominator will be all eligible ED encounters (see **Inclusion criteria**, above). Encounters resulting in an inpatient admission will be excluded from the numerator and denominator.

3b. Percent of encounters with an ED revisit measured at 7 days. The numerator will be an ED encounter at any facility included in the INPC database within 7 days of an ED encounter at an intervention or comparator site. ED revisits may serve as the index visit for subsequent revisits. The denominator will be all eligible ED encounters (see **Inclusion criteria**, above). Encounters resulting in an inpatient admission will be excluded from the numerator and denominator.

3c. Percent of encounters with an ED revisit measured at 30 days. The numerator will be an ED encounter at any facility included in the INPC database within 30 days of an ED encounter at an intervention or comparator site. ED revisits may serve as the index visit for subsequent revisits. The denominator will be all eligible ED encounters (see **Inclusion criteria**, above). Encounters resulting in an inpatient admission will be excluded from the numerator and denominator.

1. Percent of ED encounters with primary care visit within 7 days of an ED encounter. The numerator will include all ED encounters with a completed family medicine, internal medicine, OBGYN, or geriatrician visit^64^ within 7 days of the ED visit. The denominator will be all eligible ED encounters (see **Inclusion criteria**, above).

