**Other pre-specified outcome measures**

1. Percent of ED encounters where the HRSN CDS intervention was accessed. The numerator will include encounters with access of the social needs section (containing the risk prediction scores) of the Health Dart CDS during the study visit (defined as within 24 hours). Access will be defined as record of the end user visiting the HRSN page in the system user logs. The denominator will be all eligible ED encounters (see **Inclusion criteria**, above). Limited to the intervention site only.
2. Percent of ED encounters where the CDS platform (Health Dart) was accessed. It is possible that our study may increase usage of the overall CDS platform, but not the HRSN intervention portion. The numerator will include encounters with access of CDS platform (Health Dart) during the study visit (defined as within 24 hours). Access will be defined as record of the end user visiting initiating a request to the Health Dart application from the EHR. Any portion of the Health Dart platform (not just the health-related social needs section) is included. The denominator will be all eligible ED encounters (see **Inclusion criteria**, above). Limited to the intervention site only.
3. **Statistical Considerations**

**Power and Sample Size.** This study's sample size is fixed at the number of ED encounters among eligible adult patients at IU Health Methodist and the matched weighted comparison group. Based on historical data, the intervention site served an average of 2,930 adult patients monthly. According to national estimates, we assumed approximately 15% of these visits would be excluded based on disposition to inpatient admission, a transfer, or death23 or were at an Emergency Severity Index level 170. In the past 12 months (01DEC2023 to 30NOV2024), the average 7-day revisit rate for the intervention site was 5.5% and 30-day revisit rate was 10.5%. These were the only outcomes available for preliminary analyses and served as the range of our outcomes. We used PASS version 24’s test for two proportions in a repeated design71 to estimate the power for the above parameters and detect an odds ratio of 0.90 to 0.50. We assumed 18 time points (9 pre and 9 post) and compound symmetry.

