With a monthly sample of 2,400 at the intervention site, we would have >80% power to detect an odds ratio of 0.75 if the readmission rate in the comparison group was 5.5%. For a readmission rate of 10.5%, we could detect an odds ratio of 0.80 with >80% power. Even if we excluded half of the intervention site patients, our sample size would still be sufficient to detect an odds ratio of 0.70 with 80% power.

1. **Analytic Plan**

We will describe the study sample using proportions and means. Our primary analysis will be a DiD approach comparing patient-encounter outcomes at the CDS intervention site with a propensity score weighted sample from other EDs. As our primary strategy we adopt an intention to treat analysis approach where all eligible encounters at the intervention ED site will be considered as having been exposed to the treatment regardless of actual use of the CDS. The following weighted regression model will estimate the probability of each outcome:

$${Outcome}_{it}=\alpha_{0}+ \beta_{1}{Treat}_{i}+ \gamma{Post}_{t}+ \delta_{rDD}\left( {Treat}_{i}*{Post}_{t} \right)+Z_{it}+\varepsilon_{it}$$

Patient-encounters are indexed by $i$ and time by $t$. ${Outcome}_{it}$ is a binary indicator representing each study outcome. ${Treat}_{i}$ is a binary indicator of inclusion in the CDS intervention group, i.e., patient- encounters at IU Health Methodist ED. ${Post}_{t}$ is a dummy variable indicating all post-intervention go-live months. $\delta_{rDD}$is the DiD estimator and will test our hypotheses that the CDS intervention is associated with each outcome. $Z_{it}$ is a set of patient-level, time varying adjustment covariates. $\varepsilon_{it}$ is the error term. Standard errors will be robust clustered at the highest level feasible; specifically, we will check for clustering at the clinician and patient levels and adjust accordingly. As described above, all observations will be weighted using the propensity score derived weights. We will compare the weighted model with the unweighted model. Given the length of panel, we will also check for, and correct for, autocorrelation as needed.

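### Visits ending in transfer out are deducted in the sample-size text but not excluded by the eligibility criteria, so a non-admitted arrival at the receiving ED can count as a revisit

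*Protocol*

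**What the plan says.** **Eligibility Criteria, Patients.** Besides critical illness or injury, the list excludes patients who "Have been transferred from another inpatient facility or died during the ED encounter" and "ED visits resulting in hospital admissions". The transfer criterion concerns where the patient came from, and only when that was an inpatient facility. No criterion concerns a visit that ends in transfer elsewhere.

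**Statistical Considerations, Power and Sample Size.** The monthly sample is derived on the assumption that about "15% of these visits would be excluded based on disposition to inpatient admission, a transfer, or death", or by ESI level 1. Disposition describes how a visit ends, so this text deducts transfers out.

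**Secondary outcomes, 3a-3c.** For 3a, "The numerator will be an ED encounter at any facility included in the INPC database within 3 days of an ED encounter". The index visit may be at Methodist or at one of the comparator EDs; 3b and 3c repeat the rule for 7 and 30 days. The denominator is all eligible encounters. Encounters that end in inpatient admission are removed from numerator and denominator. There is no minimum gap after the index visit and no exception for transfers. A revisit may itself serve as an index visit.

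**The concern.** The eligibility list defines the denominator of every effectiveness outcome, and it does not describe the sample that the power paragraph assumes. Two analysts, one following each text, would build different cohorts.

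The revisit outcomes are where this matters most. Suppose a patient is seen at one ED, sent to a second ED in the INPC network, and discharged from there. Under the written rules the first visit is an eligible index encounter and the second arrival is a revisit, although the patient never went home in between. Nor is the second arrival removed as an index encounter by the transfer criterion, which names only an inpatient facility as the source, so it may start a new index encounter. Such events say nothing about whether the CDS intervention prevents a return to the ED.

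**Working it through.** **1. The planned sample.** Inputs, all from Power and Sample Size: "the intervention site served an average of 2,930 adult patients monthly", about 15% excluded, and 2,400 per month used for power.

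- 2,930 × (1 − 0.15) = 2,490.5 per month, against 2,400 stated.
- 2,400 corresponds to 1 − 2,400/2,930 = 18.1% excluded.

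The stated figure is the lower, hence conservative, one. Transfers are already inside the deduction, so excluding them does not reduce the planned sample. The stated power cannot be reproduced exactly, because the significance level and the correlation value are not given, but nothing below depends on it.

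**2. The texts side by side.**

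| Case | Eligibility list | Power paragraph |
|---|---|---|
| Transfer in from an inpatient facility | excluded | not described as such |
| Transfer in from another ED | not excluded | not described as such |
| Disposition: transfer out | not excluded | deducted |
| Disposition: admission | excluded | deducted |
| Death in the ED | excluded | deducted |

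**3. Effect on the level of the revisit rate.** Let *p* be the revisit rate without the artefact, *t* the share of index visits transferred out, and *a* the share of those with a countable (non-admitted) receiving-ED encounter. Then

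observed rate = (1 − t)p + t[a + (1 − a)p] = p + t·a·(1 − p).

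The protocol gives 5.5% (7 days) and 10.5% (30 days) for the intervention site. It does not say how those figures treated transfers; here they are taken as free of them. It gives neither *t* nor *a*, so both are assumed.

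- 7 days, t = 1%, a = 50%: 0.01 × 0.5 × 0.945 = 0.47 points, so 5.5% becomes 5.97%. About 8% of counted revisits (0.47/5.97) would be artefact.
- 7 days, t = 0.5% to 3%, a = 10% to 100%: 0.05 to 2.8 points.
- 30 days, same ranges: 0.04 to 2.7 points.
- 3 days: no baseline is given. A 3-day revisit is also a 7-day revisit, so *p* is at most 5.5%; at t = 1%, a = 50% the addition is 0.47 to 0.50 points on a base no larger than the 7-day rate.

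**4. The scale to judge it by.** Odds ratio 0.75 at 5.5%: odds 0.055/0.945 = 0.0582; × 0.75 = 0.04365; 0.04365/1.04365 = 4.18%. The difference is 1.32 points. By the same steps, odds ratio 0.80 at 10.5% gives 8.58%, a difference of 1.92 points.

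**5. Constant transfer share.** If *t* and *a* are the same in both groups and periods, the added amount cancels on the risk-difference scale and a true difference is multiplied by (1 − t·a). At t = 1%, a = 50%: 1.32 × 0.995 = 1.31 points. On the odds-ratio scale a true 0.75 is observed as 0.770; over the whole assumed range it is observed as 0.752 to 0.835. A true 0.80 at 30 days is observed as 0.801 to 0.841. This is dilution toward no effect.

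**6. Differential change.** If the transfer share changes by Δt more in one group than in the other between periods, the DiD estimate shifts by Δt·a·(1 − p). With an assumed Δt of 0.5 points at 7 days:

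- a = 50%: 0.005 × 0.5 × 0.945 = 0.24 points, or 18% of 1.32.
- a = 100%: 0.005 × 1 × 0.945 = 0.47 points, or 36% of 1.32.

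A relative rise at the intervention site would hide a benefit; a relative fall would imitate one.

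**The case against.** The best defence is that the mismatch is loose wording. The power paragraph names the same items as the eligibility list (admission, transfer, death, ESI level 1), rests on national estimates, and reads as a summary of that list. Hypothesis 4 counts from discharge, which suits a treat-and-release cohort. That probably describes the intention. It does not settle the rule, because denominators are taken from the eligibility list, and that list leaves transfers out in the cohort.

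The admission exclusion might be read to cover a transfer that leads to admission elsewhere. The text does not say so, and that reading would not reach patients discharged by the receiving ED, who are the ones that generate false revisits.

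Other objections stand and limit the point:

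- A reader might infer that any change in transfer patterns, or the mere fact that EDs transfer at different rates, would be read as a CDS effect. The model in the Analytic Plan does not support that. A stable site difference goes into the Treat term and a common change over time into the Post term; only a differential change reaches the interaction.
- A reader might take the inflation of the rate as the size of the bias. It is not: the level mostly cancels, the transfer share is assumed, and receiving encounters that end in admission are already removed from the numerator.
- That one arrival can be both a revisit and a new index encounter is an explicit rule in 3a-3c, not a by-product of transfers.
- The 1.32 points is a detectable difference from the power grid, not a predicted effect, and the documents give no reason to expect transfer patterns to change differently between sites.
- How transfers are recognised in the data is normally left to the SAP, which is not at hand.

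**Conclusion.** The contradiction is real: the eligibility list excludes transfers in from an inpatient facility, the power paragraph deducts visits with a transfer disposition, and the two cannot both describe the analysed sample. Followed literally, 3a-3c score an ED-to-ED transfer discharged by the receiving ED as a revisit.

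The size cannot be fixed from the protocol. With 1% transferred and half countable, the 7-day rate rises by about 0.5 points, and the DiD estimate is only slightly diluted if that share is constant. Bias arises only with a differential change; the assumed 0.5-point example moves the 7-day estimate by 0.24 to 0.47 points against 1.32. Both rest on assumed shares.

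Only the secondary revisit outcomes are affected in this way. For screening, referral and primary care follow-up, retained transfers change the denominator only. A reader might infer that the primary outcomes are biased by false events or that the planned sample is too small; the documents support neither. The point should be corrected, but it does not undermine the design.

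**What to change.** 1. Add to the patient exclusions: index visits with an ED disposition of transfer to another acute-care facility. The eligibility list and the power paragraph then agree.
2. State in 3a, 3b and 3c that an ED arrival completing a transfer from the index encounter is not a revisit.

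The operational rule for linking the two records can be left to the SAP, once it is confirmed which fields the INPC data hold for this purpose.

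The cost is one exclusion line and one sentence in each revisit outcome. The few encounters lost are already deducted in the sample-size text. This version lists recruitment as pending, so the wording can be settled before post-go-live outcomes are analysed.

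### Eligibility drops visits that end in admission, a disposition reached after the risk score is available, and outcomes 3a-3c read literally also leave out return ED visits that end in admission

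*Protocol*

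**What the plan says.** Protocol, Eligibility Criteria (Patients) excludes "ED visits resulting in hospital admissions". It also excludes patients who "Have been transferred from another inpatient facility or died during the ED encounter".

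Protocol, Intervention puts the start of exposure at arrival: "HRSN risk scores are triggered by patient registration at the ED", and "Within 20 seconds of patient registration, Indiana HIE passes an HL7 message with patient identifiers". The score is seen on demand: "End users selecting the social needs menu will be presented with a likelihood score".

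Protocol, Analytic Plan labels the main analysis intention to treat because "all eligible encounters at the intervention ED site will be considered as having been exposed to the treatment", whether or not anyone used the CDS. Protocol, Measures and Outcomes builds the denominator of both primary outcomes and all secondary outcomes on eligible encounters. Revisit outcomes 3a-3c add: "Encounters resulting in an inpatient admission will be excluded from the numerator and denominator".

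**The concern.** An intention-to-treat set is normally fixed by facts that precede exposure. Here membership is settled by a disposition that comes after the score is available to the treating ED clinicians. The score concerns housing, transport, food, money and legal involvement, and the ED has social workers on staff. Such information could plausibly bear on whether a patient goes home. If it does, the set of discharged patients changes in the intervention-site post-period cell and in no other. A difference-in-difference removes fixed site differences and shared trends, but not a change of this kind. The percentages screened, referred and revisiting could then move through case mix alone.

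A treat-and-release restriction is natural for revisits and for primary care follow-up after discharge. The two primary outcomes need it less, because screening, and referral within 24 hours, can be recorded whatever the disposition.

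The sentence in 3a-3c raises a second, more concrete problem. The numerator is defined as the later ED encounter. Taking admitted encounters out of the numerator therefore removes a return visit that ends in admission. A shift towards admission at the return visit would look like fewer revisits.

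**Working it through.** **Order of events.** Registration triggers the score; the score can be viewed during the visit; disposition follows; eligibility is then settled. Age, severity level 1 at presentation and transfer in from an inpatient facility are known on arrival. Admission and death in the ED are not.

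**Inputs from Protocol, Power and Sample Size.** 2,930 adult patients a month; about 15% excluded (admission, transfer, death and severity level 1 together); 30-day revisit rate 10.5%; detectable odds ratio 0.80 at that rate; monthly sample 2,400.

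**Plan's own figure.** 2,930 x 0.85 = 2,490, against the stated 2,400, which would imply 1 - 2,400/2,930 = 18.1% excluded. The gap is on the cautious side and does not affect this point. I use N = 2,490.

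**Planned effect.** Odds at 10.5% are 0.105/0.895 = 0.1173. Multiplied by 0.80 they are 0.0939, a rate of 8.58%. The difference is 1.92 points.

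**Artefact with no true effect.** Suppose k visits with event risk p move into (+) or out of (-) the eligible set, whose base rate is b. The exposed cell then moves by

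±k(p - b)/(N ± k)

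and the other three cells do not move, so this is also the shift in the difference-in-difference. The shift of 1% of arrivals, k = 29.3, is an assumption, as are all values of p and the base referral rates. Changes are in percentage points.

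| Outcome | b | p | Moved in | Moved out |
|---|---|---|---|---|
| 30-day revisit | 10.5% | 20% | +0.11 | -0.11 |
| 30-day revisit | 10.5% | 30% | +0.23 | -0.23 |
| Referral | 5% | 50% | +0.52 | -0.54 |
| Referral | 10% | 50% | +0.47 | -0.48 |

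For revisits, 0.11/1.92 = 6% and 0.23/1.92 = 12% of the planned effect. A 2% shift roughly doubles each entry.

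**Effect on false positives for 30-day revisit.** Here a share s of visits that would have been discharged is admitted instead, with revisit risk RR times the average. The calculation assumes four independent cells of 9 x 2,400 encounters, a two-sided 5% test and the normal approximation. The new rate is 0.105(1 - s x RR)/(1 - s).

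| s | RR | Rate | Odds ratio | False-positive rate |
|---|---|---|---|---|
| 1% | 2 | 10.39% | 0.989 | 5.7% |
| 2% | 3 | 10.07% | 0.955 | 18% |
| 5% | 2 | 9.95% | 0.942 | 27% |

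If marginal admissions were sent home instead, the sign reverses (s = 5%, RR = 2: 11.0%, odds ratio 1.054).

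**How large these shifts are.** Excluded visits number about 2,930 x 0.15 = 440 a month. A 1% shift of arrivals is 29.3/440 = 6.7% of them. A 5% shift of discharged visits is about 125 visits, or 28%.

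**Outcomes 3a-3c.** Let R be the rate of return to an ED with any disposition and a the share of returns that end in admission. Read literally, the recorded rate is R(1 - a). If R is 10.5% (assumed here to count all dispositions), each 1-point rise in a lowers the recorded rate by 10.5% x 0.01 = 0.105 points, with no fewer returns. The protocol does not give a.

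**The case against.** The mechanism is not documented. The protocol speaks of awareness and of connecting patients to services, and nowhere says that the CDS alters admission. Use is voluntary, the score appears only when a user opens the menu, and the plan itself provides for usage too low to model. Every illustrative shift and risk is assumed and must be net in one direction. Even 1% of arrivals is a sizeable relative change for an optional menu. All of this stands, and it caps the weight of the point.

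The referral example is partly circular. If awareness changed a patient's disposition, some of the assumed 50% referral chance is the intended effect. So the half-point figure overstates pure case mix.

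The exclusion applies at all sites and in both periods. Weights, covariates and the planned stratification by risk category would absorb part of a shift in measured need. This is right, but these tools work within the selected encounters and cannot fully undo an induced change in who is selected.

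An admission check may sit in an SAP that is not shown, so its absence from the protocol is not counted as a fault. Eligibility and denominators, however, are fixed here.

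The sentence in 3a-3c may be meant for index visits only. That is possible. But admitted index visits are already ineligible, so on that reading the sentence adds nothing, and on the literal reading it removes returns. The text should settle it.

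A reader might go further and infer that clinicians will have seen the score before disposition, or that the primary results are biased. The documents support neither: they show that the score is available, not that it is viewed, and that selection is possible, not that it occurs.

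**Conclusion.** The point holds in limited form. The analysis conditions on a disposition reached after exposure becomes possible, and the difference-in-difference does not protect against a CDS-induced change in the one exposed cell. Size and direction are unknown. Under the assumed risks, the 30-day revisit artefact is 6-12% of the planned effect if 1% of arrivals change disposition. It becomes material only with shifts of roughly 2-5% among patients whose risk differs strongly. The 3a-3c point needs no assumption about the index visit: as written, return visits ending in admission can be left out of the count. Together these justify a cheap improvement, not a redesign.

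**What to change.** 1. In 3a-3c, state that the admission exclusion applies to the index visit only, and that a return ED visit counts whatever its disposition.
2. Run the same weighted difference-in-difference with hospital admission as the outcome, among adult arrivals eligible on facts known at presentation. Report it beside the main results. An estimate near zero with a narrow interval would largely answer the concern about net shifts.
3. Keep the present definitions and denominators of outcomes 1 and 2 as primary. Add a sensitivity analysis on all such arrivals that counts screening or referral made during the ED stay, so that inpatient activity does not enter. This is narrower than the 24-hour referral window, so it should not replace the primary definition.

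The treat-and-release restriction on index visits stays for outcomes 3 and 4. The cost is that admitted encounters must be kept in the extract and a few extra regressions reported. Recruitment status is pending, so all three can still be prespecified.
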